### 2.8. Risk and Adverse Events

While no significant adverse events have been reported for studies of this nature, and the study and the intervention are low risk, participants might experience events such as gastrointestinal discomfort and weight gain caused by the addition of milk, discomfort caused by venepuncture, and low blood sugar due to fasting. Participants were provided information about these risks before they provided informed consent for the study. Management actions were put in place such as referral to a dietetics student, supervised by a registered dietitian, for dietary advice and support, the engagement of trained phlebotomists, and the provision of snacks and beverages after blood draws.

Adverse events were monitored and recorded by the research team, and the research team assessed and managed the condition. In the event of significant adverse events, the participant would be referred to the study clinician for assessment and management plan, and the event recorded in the case report form.

## 3. Study Outcomes and Measurements

### 3.1. Weekly Questionnaires

Participants completed weekly questionnaires on the study app or on paper from baseline until the end of the 12-week intervention period. These weekly questionnaires are described briefly below.

#### 3.1.1. Gastrointestinal Syndrome Rating Scale (GSRS)

The primary outcomes are between-group differences in abdominal pain scores and bowel comfort scores from baseline to week 12, measured using the abdominal pain domain in the GSRS. Upon enrolment, participants filled out the GSRS on a weekly basis. The GSRS is a validated questionnaire that uses a 7-level Likert scale (1–7) to assess the frequency and intensity of gastrointestinal symptoms experienced in the past 7 days [63]. It contains 15 items divided into five domains covering the gastrointestinal system: Reflux, Abdominal pain, Indigestion, Diarrhea, and Constipation. A higher score represents more frequent and/or severe symptoms experienced by the patients. Significant responders to the intervention will be those reporting at least a 0.6 reduction in abdominal pain severity score, the minimal important difference [64], compared to baseline.

#### 3.1.2. Patient-Reported Outcomes Measurement Information System (PROMIS): Anxiety and Depression

PROMIS is a set of measures covering different domains that evaluate and monitor physical, mental, and social health [65]. Specific domains can be picked to be integrated into diverse data collection tools. In this case, two scales from the psychosocial domain, anxiety and depression [66], were used to evaluate psychosocial symptoms in the past seven days in detail. This evaluation allows the examination of potential associations or confounding with gastrointestinal symptoms or gut microbiota parameters.

#### 3.1.3. Leeds Sleep Evaluation Questionnaire (LSEQ)

LSEQ is an instrument used to monitor self-perceived changes in sleep which consists of 10,100 mm Visual Analog Scales [67]. The questionnaire was administered on paper. The questionnaire contains questions related to ease of initiating sleep, quality of sleep, ease of waking and behavior following wakefulness. This allows the study of the association between milk intake and sleep quality.

#### 3.1.4. Sensory and Emotional Assessments

After study allocation, participants in the milk groups completed a weekly sensory survey where they rated their overall liking and specific liking of the flavor, texture, and aftertaste of their allocated study milk on a nine-point hedonic scale [68]. A circumplex question in which they indicate the level of pleasantness and arousal they experience after having their study milk assessed their emotional response to their study milk [69]. These assessments provide insights into how participants perceived and experienced their study milk and its impacts on milk intake.

#### 3.1.5. Milk-Specific Food Frequency Questionnaire

Participants recorded the type and quantity of milk and milk-containing products (e.g., coffee, tea, and hot chocolate.) they consumed outside the study. This allows the assessment of habitual non-study milk intake.

### 3.2. Daily Questionnaires

Participants completed the following daily questionnaires on the study app or paper from baseline until the end of the 12-week intervention period.

#### 3.2.1. Bowel Movement Diary

Participants recorded the frequency, spontaneity and completeness of their bowel movements, ease of defecation or level of straining and stool form according to the Bristol Stool Scale. This provides a comprehensive record of their bowel habits and captures any changes that may have occurred throughout the study.

#### 3.2.2. Compliance Diary

After randomization, participants in the milk groups recorded their consumption of their assigned milk. This provides a comprehensive record of their compliance with study instructions and captures any changes that may have occurred throughout the study.

### 3.3. Dietary Assessment

Participants completed three-day weighed diet records [70] during the week prior to their baseline visit and the week prior to their final visit (week 12). The three recordings were randomly assigned (two weekdays and one weekend day). This will be used to assess baseline protein intake and the impact of increased ruminant milk consumption on protein intake. The data will also be used to determine associations between diet and other study outcomes.

Participants were given a set of kitchen scales, a photo booklet depicting different portion sizes, and verbal and written instructions on how to measure and record their diet. When they came in for their baseline and final visits, the research team reviewed their diet records to check whether adequate details have been provided and whether there were any issues with recording. The diet record data will be entered into FoodWorks11 (Xyris, Brisbane, Australia) by a nutrition student trained in dietary assessment. The New Zealand food composition data NZ FOODfiles 2016 (Plant and Food Research Ltd., Palmerston North, New Zealand) will be used to estimate energy and nutrient intake and the data will also be adjusted for day-to-day variations using established procedures.

### 3.4. Physical Activity and Sleep Assessment

Participants were provided with an accelerometer, ActiGraph wGT3X-BT, to be worn on their non-dominant wrist for seven consecutive days, one week prior to baseline (day-7) and one week prior to week 12, to assess habitual physical activity and sleep patterns. The accelerometers were initialized to record data at a sampling frequency of 30 Hz in three axes: vertical, mediolateral, and anteroposterior [71], using ActiLife software (V6.13.3 Lite Edition, ActiGraph, FL, USA). Participants were asked to keep the accelerometer on at all times except during water-based activities such as showering, bathing, and swimming. They were also given a physical activity and sleep diary for recording instances when they removed the accelerometer for more than 5 min, activities that may not be tracked accurately by the accelerometer (e.g., swimming, biking, weight training), along with their respective intensities as well as sleep-related information such as the time they tried to go to sleep, the time they woke up, and the time they got out of bed. Days that consist of a minimum of 10 h wear time during waking hours or a minimum of 20 h wear time with imputed physical activity (physical activity recorded in the diary) and at least 2 h of sleep will be considered valid and data sets containing 3 or more valid days will be used for analysis [72].

### 3.5. Clinical Measurements

#### 3.5.1. Anthropometry

At the screening visit, the participants’ height and weight were measured to calculate body mass index (BMI) as weight in kilograms per height in meters squared. At the baseline visit (week 0) and final visit (week 12), the participant’s height, weight and waist circumference were measured to monitor any changes in weight and central adiposity with the addition of 500 mL milk each day.

All measurements were taken according to guidelines/protocols set out by the New Zealand Ministry of Health [73]. Briefly, height was measured to the nearest millimeter using calibrated stadiometers, weight was measured to the nearest 0.01 kg using calibrated scales and waist circumference was measured at the narrowest point between the lower costal border and the top of the iliac crest using anthropometric tape measures. All measurements were taken with shoes removed and light clothing. All anthropometric measurements were taken in duplicate, with a third measurement taken should the first two differ by 10% and the average value taken.

#### 3.5.2. Body Composition

A whole-body DEXA scan was performed at baseline and week 12 to assess body composition (fat mass and lean body mass) to support anthropometric measurements in the event of body weight changes. Dunedin participants were scanned on the Lunar iDXA scanner (GE HealthCare, Madison, WI, USA) while Christchurch participants were scanned on the Lunar Prodigy scanner (GE HealthCare, Madison, WI, USA), In preparation for the scan, participants were asked to remove any metal artifacts (e.g., jewelry, clothing with metal fasteners) from their person and keep on light clothing or be given a hospital gown to wear. They were positioned on the scanning table in a supine position with their arms by their side, parallel to but not touching the body, palms facing their legs and legs fully extended [74]. Offset scanning was performed for participants who did not fit in the scanning field of view, as per the Official Position of the ISCD [74].

#### 3.5.3. Blood Pressure

Blood pressure was taken at baseline visit (week 0) and final visit (week 12) according to the guidelines set by the Australian Expert Consensus [75] using an automated blood pressure measurement system with an appropriately sized upper arm cuff. Participants were seated with their back and arm supported in a relaxed positioned, legs uncrossed, feet flat on the floor, and the cuff at heart level. Their blood pressure was measured 3 times, and the average value taken.

#### 3.5.4. Functional Tests

A timed 5 m timed walk test was performed at baseline visit (week 0) and final visit (week 12) to assess functional mobility. Briefly, a pathway measuring 7 m was measured and marked at 0 m, 5 m, and 7 m with bright tape. Participants were instructed to stand behind the 0 m mark with the tip of their shoes just touching the mark and given a cue (“1, 2, 3, go”) to start walking from the 0 m mark to the 7 m mark without assistance or with assistive devices if necessary (which was consistent and documented from test to test) [76]. A researcher started the timer when the toes of the leading foot crossed the 0 m mark and stopped the timer when the toes of the leading foot crossed the 5 m mark. The test was repeated 3 times, and the average value was taken.

A handgrip strength test was performed at baseline and week 12 using a Jamar Plus+ Digital Hand Dynamometer (Performance Health, Warrenville, IL, USA). Participants were seated with their elbow by their side and flexed to 90 degrees and asked to hold on to the dynamometer set at position 2 from the inside with their dominant hand [77]. They were asked to squeeze the dynamometer as hard as possible and three successive measurements recorded to the nearest 1 kg were taken with 10–20 s rest between subsequent measurements, and the average value taken [77].

### 3.6. Biological Measurements

#### 3.6.1. Blood Samples

During the baseline and final visits, fasting blood samples were collected from participants by trained phlebotomists into two BD Vacutainer^®^ serum tubes for trace element determination with K_2_EDTA, two BD Vacutainer^®^ lithium-heparin tubes, and one BD Vacutainer^®^ K_2_EDTA tube (Becton, Dickinson and Company, Franklin Lakes, NJ, USA). Postprandial blood samples were collected from participants who took part in the sub-study into one BD Vacutainer^®^ lithium-heparin tube, one BD Vacutainer^®^ K_2_EDTA tube and one BD Vacutainer^®^ P800 tube (Becton, Dickinson and Company, Franklin Lakes, NJ, USA). The collected samples were kept on ice and processed within an hour. After aliquots of whole blood were taken from the lithium heparin tubes used in the main study, all vacutainers were centrifuged at 1500× *g* for 15 min at 4 °C to separate plasma from cells. Aliquots of both whole blood and plasma were then frozen at −80 °C until analysis.

Amino acids

Amino acid concentration in plasma will be analyzed as previously described [78] to examine the impact of sustained milk consumption on circulating amino acids by reverse-phase chromatography and fluorescence detection [79]. Briefly, the frozen plasma samples will be thawed, mixed with a 0.02% sodium azide solution, and centrifuged in 3000 MWCO Vivaspin 500 centrifugal concentrators (Sartorius, Goettingen, Germany) at 13,675× *g* for 40 min at 10 °C. The resulting samples will be mixed with norvaline as an internal standard solution and analyzed using an Agilent 1290 Infinity II HPLC system (Agilent Technologies Inc., Santa Clara, CA, USA) with automated online precolumn o-phthalaldehyde derivatization. Precolumn-derivatized free amino acids in solution will be separated on a C18 reversed-phase column and detected on a fluorescence detector set at 230 nm excitation wavelength with a 450 nm emission cutoff filter.

2.Blood lipids and Hemoglobin A1c (HbA1c)

Blood lipid (total cholesterol, high-density lipoprotein, triglycerides) and HbA1c concentrations in plasma will be analyzed to monitor potential cardiometabolic effects from increased milk consumption using a Cobas c311 Analyzer (Roche, Basel, Switzerland) according to manufacturer’s instructions. Briefly, the frozen plasma samples will be thawed, homogenized and centrifuged at 2000× *g* for 10 min before the samples are loaded into the analyzer with the appropriate reagent kits. Quality control will be performed using PreciControl ClinChem Multi 1 and 2 (Roche, Basel, Switzerland), and calibration will be carried out using Calibrator F.A.S. Proteins (Roche, Basel, Switzerland) and pooled serum. Low-density lipoprotein concentration will be calculated using the Friedwald equation [80].

3.Trace elements

Trace elements (zinc, selenium, and magnesium) concentration in serum will be analyzed using inductively coupled plasma mass spectrometry (ICP-MS) [81] to give objective markers of dietary intake and to assess changes in nutrient intake with the addition of milk to the diet. Briefly, 100 μL of thawed serum will be mixed with 200 μL of 65% nitric acid and 100 μL of hydrogen peroxide and vortexed briefly. The mixture will be incubated at 60 °C for 90 min before being cooled down with the addition of 2100 μL ultrapure water. The samples will be then vortexed and centrifuged for 3 min at 595× *g* before being loaded into an Agilent 7500ce ICP-MS (Agilent Technologies Inc., Santa Clara, CA, USA) for analysis as previously described [82].

4.Inflammatory markers

Inflammatory markers (high sensitivity C-reactive protein and α-acid-1-glycoprotein) in plasma will be analyzed to adjust for nutrient biomarkers that are altered in the presence of inflammation (e.g., serum zinc and selenium) [82] and as potential confounders of skeletal muscle strength and muscle mass [83]. Analyses will be undertaken using a Cobas c311 Analyzer (Roche, Basel, Switzerland) according to the manufacturer’s instructions. Briefly, the frozen plasma samples will be thawed, homogenized and centrifuged at 2000× *g* for 10 min before the samples are loaded into the analyzer with the appropriate reagent kits. Quality control will be performed using PreciControl ClinChem Multi 1 and 2 (Roche, Basel, Switzerland), and calibration will be carried out using Calibrator F.A.S. Proteins (Roche, Basel, Switzerland) and pooled serum.

5.Parathyroid hormone and vitamin D

Parathyroid hormone and vitamin D in plasma will be analyzed as they are potential confounders of skeletal muscle function [84] using Cobas e411 Analyzer (Roche, Basel, Switzerland) according to the manufacturer’s instructions. Briefly, the frozen plasma samples will be thawed, homogenized and centrifuged at 2000× *g* for 10 min before the sample is loaded into the analyzer with the appropriate reagent kits (Roche, Basel, Switzerland). Quality control for parathyroid hormone will be performed using PreciControl Varia (Roche, Basel, Switzerland), and calibration carried out using CalSet PTH (Roche, Basel, Switzerland) and pooled serum. Quality control for vitamin D will be performed using Vitamin D total II CalSet (Roche, Basel, Switzerland), and calibration carried out using PreciControl Vitamin D total II (Roche, Basel, Switzerland) and pooled serum.

6.Non-polar metabolites

The relative intensity of non-polar metabolites in plasma will be analyzed to identify lipid metabolites that are produced in response to the different study milks. Non-polar metabolites will be extracted from plasma as previously described [85]. Briefly, 10 μL of plasma will be mixed with 100 μL of butanol/methanol (1:1) with 10 mM ammonium formate containing a mixture of internal standards. The samples will be vortex mixed and incubated in a sonicator bath maintained at room temperature for 60 min before being centrifuged at 14,000× *g* for 10 min at 20 °C. The supernatant will then be transferred into sample vials with glass inserts for analysis. For analysis, the samples will be injected into a C18 reverse-phase column in a Shimadzu Nexera-x2 Ultra Performance Liquid Chromatography^®^ system equipped with a Shimadzu LCMS-9030 mass spectrometer (Shimadzu Corporation, Kyoto, Japan) [86]. The mass spectrometer will be operated in positive ionization mode to measure full MS1 spectra from 250 to 1250 *m*/*z* across the entire chromatogram and collect data independent acquisition (DIA) data in 20 *m*/*z* windows from 300 to 1100 *m*/*z*.

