### 3.7. Acute Sub-Study

During the baseline and final study visits, participants who consented to the sub-study consumed a bolus dose (500 mL) of their allocated milk. Sequential blood samples were drawn at 0, 60, 120, 180, 240, and 300 min to measure circulating levels of amino acids, insulin, and triglycerides.

Amino acid concentrations in plasma will be analyzed as described in Section 3.6.1. to assess the impacts of sustained milk consumption on circulating amino acid appearance. Circulating insulin and triglycerides will be assessed to determine the GlucoTRIG index of the study milks, a novel index for classifying the overall healthiness of meals based on the glycemic and lipemic responses they induce [56]. Insulin and triglycerides in plasma will be analyzed using Cobas e411 Analyzer (Roche, Basel, Switzerland) and Cobas c311 Analyzer (Roche, Basel, Switzerland), respectively, according to the manufacturer’s instructions. Briefly, the frozen plasma samples will be thawed, homogenized and centrifuged at 2000× *g* for 10 min before the sample is loaded into the analyzers with the appropriate reagent kits. Quality control for insulin will be performed using PreciControl Multimarker (Roche, Basel, Switzerland) and calibration carried out using Insulin CalSet (Roche, Basel, Switzerland) and pooled serum. Quality control for triglycerides will be performed using PreciControl ClinChem Multi 1 and 2 (Roche, Basel, Switzerland) and calibration carried out using Calibrator f.a.s. (Roche, Basel, Switzerland) and pooled serum.

During these timepoints, participants also completed a questionnaire to self-report appetite and satiety. This questionnaire, comprising eight 100 mm Visual Analog Scales, consists of questions relating to feelings of perceived hunger, satisfaction, fullness, and desire for specific food types [96]. This allows the study of potential adaptations to daily milk consumption.

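### HbA1c, an exploratory 12-week outcome, is assigned to cell-free plasma, which cannot give a valid value, while the frozen whole blood is assigned to no assay

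*Protocol article*

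**What the plan says.** Section 3.6.1 (Blood Samples) of the protocol article first describes collection and processing. Whole blood was set aside before spinning: "After aliquots of whole blood were taken from the lithium heparin tubes used in the main study", all tubes were centrifuged "to separate plasma from cells". Both materials were kept: "Aliquots of both whole blood and plasma were then frozen at" −80 °C.

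The item on blood lipids and HbA1c in the same section then says that lipid and "HbA1c concentrations in plasma will be analyzed" on a Cobas c311 according to the manufacturer's instructions. The preparation step names the specimen a second time: "Briefly, the frozen plasma samples will be thawed, homogenized and centrifuged at" 2000 × g before loading. One set of controls and one calibrator is named for lipids and HbA1c together: "calibration will be carried out using Calibrator F.A.S. Proteins", with pooled serum.

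The Introduction lists HbA1c among the exploratory cardiometabolic outcomes of the 12-week intervention, alongside blood lipids, body weight, body composition and blood pressure. Section 2.2 gives the screening limit for HbA1c as 54 mmol/mol Hb.

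**The concern.** HbA1c is glycated hemoglobin, and hemoglobin is carried in red cells. Plasma that has been separated from the cells holds only the traces released by incidental hemolysis. The article names a specimen that lacks the analyte, and does so twice: once when it states the measurement and once when it describes sample preparation. The material that does contain the analyte was frozen, but no assay described in the article is said to use it.

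This is not detail that an article can leave to a fuller protocol. It is a stated method that would fail if followed. At stake is the only glycemic marker in the 12-week cardiometabolic set. Insulin is measured only in the acute sub-study, which 9 women completed (section 2.2), so it cannot stand in for HbA1c in the main trial.

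**Working it through.** The plan states no figure to reproduce. The check compares the article's own statements and then counts the samples affected.

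**Specimen**

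| Question | What the article says | Where |
|---|---|---|
| Which specimen is named for HbA1c? | Plasma | 3.6.1, lipids and HbA1c item |
| How is it prepared? | Frozen plasma thawed, homogenized, centrifuged again; no whole-blood step | 3.6.1, same item |
| Were cells removed before plasma was stored? | Yes, by centrifugation | 3.6.1, opening paragraph |
| Was whole blood kept? | Yes, from the main-study lithium-heparin tubes, frozen | 3.6.1, opening paragraph |
| Which assay uses the whole blood? | None named: the other blood assays are assigned to plasma or serum | 3.6.1 and 3.7 |
| On what scale is HbA1c expressed? | mmol per mol hemoglobin | 2.2, screening criteria |

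A quantity expressed per mole of hemoglobin needs a specimen with hemoglobin in it. The fourth row describes such a specimen; the first two rows name one without it. No other section corrects the wording.

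**Number of values affected**

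- Ceiling: 165 women randomized (section 2.1) x 2 visits (weeks 0 and 12) = 330.
- Assuming the 15% attrition predicted in section 4.1 and all losses before week 12: 165 x 0.85 = 140.25, so 165 + 140 = 305.

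**What is not affected**

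- The primary outcome is the GSRS (section 3.1.1). The key secondary aim rests on amino acids, trace elements and protein intake (Introduction). Neither uses HbA1c.
- The sample size in section 4.1 is based on the GSRS and nutrient intake.
- HbA1c for eligibility belongs to the separate screening panel (section 2.3.1 and Table A1), which the plasma paragraph does not cover.

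**Side note on calibrators**

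The lipid and HbA1c item covers triglycerides on the Cobas c311 and says "calibration will be carried out using Calibrator F.A.S. Proteins". Section 3.7 covers triglycerides on the same analyzer and says "calibration carried out using Calibrator f.a.s. (Roche, Basel, Switzerland"), without the word Proteins. The two names differ. The article does not allow one to say which is right.

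**The case against.** The strongest reply is that this is condensed wording and not a real laboratory plan. The item invokes the manufacturer's instructions and the appropriate reagent kits. The plasma handling is a summary sentence repeated almost word for word for the inflammatory markers, for parathyroid hormone and vitamin D, and for the sub-study assays. Whole blood was set aside before spinning, in the main study only, and HbA1c is the obvious use for it. On this reading HbA1c was simply swept into the lipid paragraph.

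Most of that stands as an account of how the error probably arose. It does not make the text right. A general reference to instructions does not cancel a specific statement of specimen and preparation, and the article never assigns the whole blood to HbA1c. A reader cannot tell which specimen was used.

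Three stronger readings are tempting, and the article supports none of them:

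- A reader might infer that the 12-week HbA1c data are already lost. Section 2.1 says laboratory analyses have commenced, but HbA1c is described in the future tense. The article does not show that plasma was assayed.
- A reader might infer damage to the trial's main conclusions. HbA1c after enrolment is exploratory and feeds neither the primary outcome, the key secondary outcomes nor the sample size.
- A reader might take the shared calibrator as proof that the paragraph was copied from the protein assays, or that the triglyceride values are wrong. That would need manufacturer documents that are not at hand.

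The objection also limits the remedy. Whole blood is said to have been kept only from lithium-heparin tubes, and nothing in the article shows that frozen blood from those tubes suits the HbA1c kit.

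**Conclusion.** The point holds as a clear error in a stated laboratory method, confined to one exploratory outcome. As written, HbA1c would be measured in a specimen that cannot give a valid result. That would affect all planned week 0 and week 12 values: at most 330, and about 305 under the plan's own attrition assumption.

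The conclusion rests on two things: that the plasma wording is taken literally, and that plasma separated from cells holds essentially no hemoglobin. The first may not match what the laboratory did or will do, and a drafting slip is the likelier explanation. The correction is still worth making, because the published method is wrong as it stands and the frozen whole blood may allow the outcome to be recovered. The difference in triglyceride calibrators is a minor separate matter.

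**What to change.** - Remove HbA1c from the plasma paragraph in section 3.6.1.
- Confirm that frozen lithium-heparin whole blood is acceptable for the HbA1c kit used. If it is, state that HbA1c is measured in the whole-blood aliquots frozen at weeks 0 and 12, and give its own sample preparation, calibrator and controls.
- If HbA1c has already been run, report which specimen was used, and do not report any plasma-based values as HbA1c.
- Reconcile the calibrator named for triglycerides in section 3.6.1 with the one in section 3.7.

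The cost is one corrected laboratory paragraph, a check of kit suitability and some of the stored whole blood. No statistical analysis or sample size changes.
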